### Outcomes

A pen-and-paper survey is completed at baseline (one week prior to first ENRICH program session), eight weeks (at the end of the ENRICH program), 20 weeks from baseline, and for the intervention group only, at 12 months from baseline. At each of these time-points, participants wear a sealed pedometer for seven days and complete a step count diary.

#### Primary outcome

The primary outcome is step counts as measured by seven days of sealed pedometry, that is used to provide an average daily step count [36]. Using a sealed pedometer prevents reactivity to monitoring step counts [37]. Despite variation in step counts on different days of the week, three days is the minimum amount of pedometer data required to estimate pedometer-determined PA in a week [38]. The step count diary allows self-report of instances where the pedometer was intentionally removed (eg. swimming, vigorous sports, sleeping) and when the participant forgot to wear the pedometer.

#### Secondary outcomes

##### Physical activity levels

PA frequency and duration is measured via eight items from the Active Australia survey. The survey evaluates four types of PA in the last week: brisk walking, moderate leisure activity, vigorous leisure activity, and vigorous household or garden chores [39].

Two items assessing the frequency and duration of resistance training were purpose-designed for this study and use the same wording and format of the Active Australia survey questions.

##### Sedentary behavior

Sedentary behavior is measured using a five-item question asking about time spent sitting (hours and minutes) during the last working and non-working day in each of the following domains: (a) while travelling to and from places (e.g., work, shops); (b) while at work; (c) while watching television; (d) while using a computer at home; and (e) at leisure not including watching television (e.g., visiting friends, movies, eating out) [40].

##### Dietary intake

Dietary intake is measured using a food frequency questionnaire, the Dietary Questionnaire for Epidemiological Studies (DQES version 2) [41]. The DQES version 2 contains a list of 74 items across four main categories (1. Cereal foods, sweets & snacks; 2. Dairy products, meat and fish; 3. Fruit; 4. Vegetables) with ten frequency response options ranging from 'Never' to 'three or more times per day'. It also contains three photographs of scaled portions for four foods (used to calculate a portion size calibrator); questions on the overall frequency of consumption of fruits and vegetables (used to calibrate the overestimation of these foods in the food list); and questions on consumption of foods such as bread that do not fit easily into the frequency format. Three questions covering alcohol consumption are also included as part of the DQES [41].

##### Waist circumference

Participants are asked to measure and report their own waist circumference, using standardized instructions [42]. Self-reported waist circumference has been reported as a satisfactory and reliable proxy for objective circumference measures [43].

##### Body mass index (BMI)

Participants report their height and weight, to allow calculation of body mass index. Data from an Australian study reports strong correlations between self-report and clinic measurements, with a trend for self-reported height to be over-estimated (especially in those aged 65 or older), and self-reported weight to be under-estimated [44].

##### Quality of life

Quality of life is assessed using the Medical Outcomes Study Short-Form-12 version 2: a 12-item measure evaluating quality of life across eight health domains: physical functioning (two items), role limitations due to physical health problems (two items), bodily pain (one item), general health perceptions (one item), vitality (energy/fatigue) (one item), social functioning (one item), role limitations because of emotional problems (two items), and general mental health (two items) [45]. These items can be used to calculate two subscales: physical and mental summary scales.

##### Social support

Social support is assessed using the 19-item Medical Outcomes Study Social Support Scale and assesses five domains of social support: informational support (four items), affection (three items), tangible support (four items), emotional support (four items), and positive social interaction (four items) [46].

##### Social cognitive mediators of physical activity

Hypothesized social cognitive mediators of PA behavior are assessed using existing validated scales. Due to a lack of validated measures for assessing mediators in relation to diet, these were not included in the survey.

An eight week time reference is provided for all the following social cognitive constructs. "Regular physical activity" is defined as *"achieving at least 30 minutes of moderate or vigorous-intensity activity on most, preferably all, days of the week" *which is consistent with national guidelines for Australian adults [47].

*Behavioral Goal *is assessed by asking participants on a scale of 0 per cent to 100 per cent, "How likely is it that you will do regular PA within the next eight weeks?" [48].

*Self-Efficacy *is measured with a nine-item scale [49]. Participants are asked to rate their confidence (*1 *= *not at all confident *to *5 *= *extremely confident*) that they could participate in regular PA over the next eight weeks when: a little tired; in a bad mood or feeling depressed; doing it by themselves; it became boring; there are no noticeable improvements in fitness; having other demands; feeling stiff or sore; there is bad weather; or having to get up early even on weekends.

*Outcome Expectations *are measured with five items [49]. The items in the scale assessed the extent to which individuals agree or disagree (*1 = strongly disagree *to *5 = strongly agree*) that participating in regular PA over the next eight weeks would for them: reduce tension or manage stress; feel more confident about one's health; sleep better; have a more positive outlook; or help control weight.

*Impediments *are measured with five items [49]. The items for this scale assess the extent to which individuals agree or disagree (*1 = strongly disagree *to *5 = strongly agree*) that participating in regular PA over the next eight weeks would for them: take too much of my time; have less time for my family and friends; make one too tired because of other daily responsibilities; make one worry about looking awkward if others saw them being physically active; or cost too much money.

*Social Support *is measured using a two-item scale [48]. Participants are asked whether over the next eight weeks people in their social network are likely to help them participate in regular PA, and whether they feel that someone in their social network will provide the support they need in order to be regularly physically active.

##### Demographics

The following demographic information is collected at baseline: gender, year of birth, postcode, marital status, education, current employment, current family income, and smoking status.

##### Health status

At baseline, participants are asked six questions about their health and service use (use of any nutrition and PA support service, diagnosed with chronic health problems, whether they are a cancer survivor, carer, or both, and if a carer, relationship to the cancer survivor), and four questions about cancer diagnosis (type of cancer, when diagnosed, treatments received, status of cancer).

##### Health Education Impact Questionnaire

Cancer survivors are asked to complete the 40-item Health Education Impact Questionnaire (heiQ). The heiQ provides a broad profile of the potential impacts of patient education programs [50] across eight domains: health directed behavior (four items); positive and active engagement in life (five items); emotional well-being (six items); self-monitoring and insight (six items); skill and technique acquisition (four items); constructive attitudes and approaches (five items); social integration and support (five items); and health services navigation (five items) [50].

### Process evaluation

Participant evaluation of the ENRICH program and sessions is measured via a participant program evaluation form (to be completed by participants at the final ENRICH session), and audit of participant attendance lists. The program evaluation form consists of nine questions from the course evaluation module of the heiQ [51]. A further eleven questions evaluating the program were purpose-designed by the research team.

ENRICH program facilitators are asked to provide their feedback on each of the sessions via pen-and-paper form. This enables the facilitators to reflect on any aspects of the program content that did or didn't work; any particular issues not well addressed; and whether or not there were any issues affecting the group sessions.

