## Abstract

**Background:**

The Exercise and Nutrition Routine Improving Cancer Health (ENRICH) study is investigating a novel lifestyle intervention aimed at improving the health behaviors of adult cancer survivors and their carers. The main purpose of the study is to determine the efficacy of lifestyle education and skill development delivered via group-based sessions on the physical activity and dietary behaviors of participants. This article describes the intervention development, study design, and participant recruitment.

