**Methods/Design:**

ENRICH is a randomized controlled trial, conducted in Australia, with two arms: an intervention group participating in six, two-hour face-to-face sessions held over eight weeks, and a wait-list control group. Intervention sessions are co-facilitated by an exercise physiologist and dietician. Content includes healthy eating education, and a home-based walking (utilizing a pedometer) and resistance training program (utilizing elastic tubing resistance devices). The program was developed with reference to social cognitive theory and chronic disease self-management models. The study population consists of cancer survivors (post active-treatment) and their carers recruited through community-based advertising and referral from health professionals. The primary outcome is seven-days of sealed pedometry. Secondary outcomes include: self-reported physical activity levels, dietary intake, sedentary behavior, waist circumference, body mass index, quality of life, and perceived social support. The outcomes will be measured at baseline (one week prior to attending the program), eight-weeks (at completion of intervention sessions), and 20-weeks. The intervention group will also be invited to complete 12-month follow-up data collection. Process evaluation data will be obtained from participants by questionnaire and attendance records.

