Little is known about the lifestyle behaviors of the carers of cancer survivors. An Australian study reported that for people with a friend or relative diagnosed with cancer, the diagnosis may have been a cue to make positive diet improvements and increase PA [27]. However, research suggests no difference between carers and non-carers on fruit and vegetable consumption, smoking status, alcohol consumption, PA, healthy body weight, or number or type of chronic illness [28,29]. Carers are likely to share many of the same behavioral risk factors as cancer survivors, and would benefit from improvements. Social support appears beneficial in helping cancer survivors make positive changes to exercise behavior [23]. Involving family members in health behavior interventions has positive effects on the patient's adherence to rehabilitation programs, and improved diet and PA behaviors [30,31].

Despite the growing evidence of the benefits and efficacy of lifestyle behaviors in promoting good health and recovery for cancer survivors, there are few services outside of the clinical setting specifically targeting cancer survivors to improve their health. Cancer survivors often report a sense of loss, and feeling "abandoned" or "cast adrift" by the health care system at the time of treatment completion [32]. There is a need to improve support and health services to assist those affected by cancer in the transition from patient to survivor. The main purpose of the present study is to evaluate the acceptability and efficacy of a healthy lifestyle (PA and diet) intervention for cancer survivors and their carers.

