### Procedure

Participants are asked to complete the pen-and-paper survey, wear their pedometer for seven-days and complete a pen-and-paper step count diary at baseline, eight, and twenty weeks from baseline (see Figure 1). In addition, the intervention group will also complete these measures at 12 months from baseline. Participants who do not return their survey, diary, and pedometer within two weeks receive one reminder call from the Project Co-ordinator. If these materials are not returned after a further two weeks, the Project Co-ordinator phones them to conduct a second and final reminder call.

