**Figure 1 F1:**
[figure not shown]
**Study flow**.

Participants are asked to attend each of the six ENRICH program sessions. Attendance records are maintained by the Project Co-ordinator.

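### The programme evaluation form is tied to the final session with no stated route for absentees, so participants' ratings risk overstating acceptability

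*Protocol article*

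**What the plan says.** The Background section of the protocol article states: "The main purpose of the present study is to evaluate the acceptability and efficacy of a healthy lifestyle (PA and diet) intervention". The Abstract's Background paragraph is narrower: "The main purpose of the study is to determine the efficacy of lifestyle education and skill development delivered via group-based sessions". Acceptability is not defined anywhere in the article, and it is not among the primary or secondary outcomes.

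The Process evaluation section gives three sources:

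- A participant form of twenty questions (nine from the heiQ course evaluation module and eleven purpose-designed), "to be completed by participants at the final ENRICH session".
- In the same sentence, "and audit of participant attendance lists".
- A facilitator report: "ENRICH program facilitators are asked to provide their feedback on each of the sessions via pen-and-paper form".

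The Abstract's Methods/Design paragraph agrees: "Process evaluation data will be obtained from participants by questionnaire and attendance records". The text after Figure 1 adds: "Attendance records are maintained by the Project Co-ordinator".

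The Procedure section describes follow-up of unreturned material: "Participants who do not return their survey, diary, and pedometer within two weeks receive one reminder call from the Project Co-ordinator". A second and final call comes after two more weeks. The evaluation form is not on that list.

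**The concern.** The form is the only place in the article where participants say what they think of the programme, and it has one collection occasion. Someone who stopped attending after session two, or who merely missed session six, gives no rating. Being present at the last session may itself depend on how acceptable the programme was, so the respondents are selected on something close to what is being measured. If people who left liked the programme less, the reported rating describes those who stayed and looks better than the view of everyone who started.

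What is at stake is how the acceptability part of the stated purpose is read. A rating that was never collected cannot be recovered by a later analysis.

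**Working it through.** **What the article fixes.** Setting the sections side by side: Process evaluation gives the occasion for the form (final session). Procedure gives the chasing system (two calls), but for other materials. Outcomes places the eight-week survey at the end of the programme, which is when the form is due, and does not make that survey conditional on attendance. So a route to absentees exists at the right time, but the form is not attached to it.

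**What the other two sources can supply.** The attendance lists identify who was absent and from which sessions. They hold no rating and no reason for stopping. The facilitator reports hold the facilitators' views. Neither supplies absentees' answers to the twenty questions.

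**Size.** The article gives no absence rate and no ratings, so there is no figure of its own on this point to reproduce. Let d be the share of starters absent from the final session, and let r_att and r_abs be the percentages of attenders and absentees who would rate the programme acceptable.

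- Rating among all starters = (1 − d) × r_att + d × r_abs
- Form rating = r_att
- Bias = d × (r_att − r_abs)

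Assumptions: 75 starters (the recruitment target per group in Statistical power and sample size); r_att = 90%; r_abs = 90%, 70% or 50%; d from 10% to 44%.

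The upper value of d is borrowed from the sample-size section. The 42 per group stated there reproduces: the two-sample t-test with a difference of 2000, SD 3200, 80% power and 5% two-sided gives 41.17, rounded up to 42. The largest loss from 75 that still leaves 42 is 1 − 42/75 = 0.44. This is a convenient bound, not a planned attrition rate, because the move from 42 to 75 also serves the secondary outcomes.

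| Absent (d) | Forms from 75 | Bias if r_abs = 90% | Bias if r_abs = 70% | Bias if r_abs = 50% |
|---|---|---|---|---|
| 10% | 67.5, about 68 | 0 | 2 points | 4 points |
| 20% | 60 | 0 | 4 points | 8 points |
| 30% | 52.5, about 52 | 0 | 6 points | 12 points |
| 44% | 42 | 0 | 8.8 points | 17.6 points |

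Example, bottom right: among all starters, 0.56 × 90 + 0.44 × 50 = 72.4%; the form shows 90%; the difference is 0.44 × 40 = 17.6 points.

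The sign follows from r_att − r_abs. If absentees would rate the programme as highly as attenders, the bias is zero; if they would rate it higher, the form understates acceptability.

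**The case against.** Several points on the other side are sound.

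- **The form is not the whole process evaluation.** A reader might infer that acceptability is collected only from people at the last session and that dropouts are left out altogether. The article does not support this. The sentence that places the form at the final session also provides for the attendance audit, in which a person who stops coming appears as a non-attender, and facilitators report on every session. The restriction applies to participants' ratings alone.
- **The link to acceptability is inferred.** The term is undefined, is not assigned to the form, and is missing from the Abstract's statement of purpose. That limits the weight of the point. It does not remove it, since no other source in the article carries participants' opinions of the programme.
- **Absence is not dropout.** A person may miss session six and remain in the programme and the trial, so the absent group is mixed and its ratings need not be low.
- **An article condenses its protocol.** A route for absentees may exist in the full document. If it does, the collection part of this point falls away. But the article does more than stay silent: it states when the form is completed and which materials are chased, and read together those statements leave absentees out.
- **An end-of-course form is ordinary practice.** That is true, and using one contradicts nothing in the article. The difficulty lies in relying on it without a supplement.

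**Conclusion.** The point holds as a risk to the participants' ratings. Followed as written, ratings come only from those present at the final session, and the remaining sources cannot supply the missing opinions or reasons. Overstatement is the plausible direction, because people who found the programme unsuitable are more likely to have stopped.

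Two stronger conclusions are tempting and should not be drawn. The first is that the rating is biased upward as a matter of fact: the article gives neither an absence rate nor any ratings, so sign and size are open. The range of 0 to about 18 points rests wholly on the assumed inputs, including that absentees rate the programme no higher than attenders. The second is that the trial's implications for service planning cannot stand: the Abstract's Discussion ties those to the results of the trial in a paragraph about efficacy, and nothing rests them on this form.

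The primary outcome, pedometer step counts, is unaffected. This is an inexpensive improvement to a supporting measure.

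**What to change.** For programmes still to run (the Setting section plans four to six more), keep the form at the final session and add to Process evaluation something like:

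*Every intervention participant who attended at least one session but did not complete the evaluation form at the final session will be given it with the eight-week survey, under the same two reminder calls, with one further question on the reason for stopping. Forms returned will be reported against the number who started and the number allocated. Ratings will be shown by number of sessions attended, alongside the attendance data, and by whether the form was completed in the session or at home.*

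Allocated participants who never attended are not asked to rate sessions they did not see. They appear in the allocated count and are not treated as having given a rating.

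The cost is a slightly longer eight-week pack for some participants, and a mixture of in-session and take-home completion. The mixture also falls between programmes, since three intervention programmes have already been conducted, so it should be reported. For those earlier programmes, report the number of forms against the numbers who started and were allocated, and read the ratings with the attendance data.

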### Procedure

Participants are asked to complete the pen-and-paper survey, wear their pedometer for seven-days and complete a pen-and-paper step count diary at baseline, eight, and twenty weeks from baseline (see Figure 1). In addition, the intervention group will also complete these measures at 12 months from baseline. Participants who do not return their survey, diary, and pedometer within two weeks receive one reminder call from the Project Co-ordinator. If these materials are not returned after a further two weeks, the Project Co-ordinator phones them to conduct a second and final reminder call.

**Figure 1 F1:**
[figure not shown]
**Study flow**.

Participants are asked to attend each of the six ENRICH program sessions. Attendance records are maintained by the Project Co-ordinator.

### Intervention development and content

ENRICH consists of four weekly sessions, followed by two fortnightly sessions. Each session consists of a mix of healthy eating information and activities, a home-based walking program information and resources (with pedometer), and a home-based resistance training program (with elastic tubing equipment, Gymstick™) with information and resources.

ENRICH program sessions are co-facilitated by an exercise physiologist (exercise specialist) and dietician who received training from members of the research team. Educational information is supplemented with practical activities (eg. food label reading), group discussion (eg. brainstorming ideas to overcome barriers to being more active), and role modelling and practice of resistance training exercises, including stretching and appropriate warm-ups and cool down. The practice is to assist participants to become familiar and comfortable with the equipment, and allows the exercise physiologist an opportunity to ensure correct technique. Participants receive a pedometer, Gymstick™, step count diary, and written resources as part of the program.

A Gymstick™ http://www.gymstick.net is a lightweight graphite shaft, with elastic tubing and foot straps that provide resistance and can be used to exercise all of the major muscle groups. It is a safe, effective and relatively inexpensive tool for a strength-based exercise program to be conducted at home [52]. Gymsticks™ are available in five different resistance levels and the load on each device can be increased by rolling the bar and shortening the elastic tubing [52].

The program content was developed by experts in each of the content areas (members of research team), with input from advisory and working group members, and reviewed by oncology dieticians and physiotherapists. The program content is structured, but allows flexibility in the delivery to allow for discussion, questions, and interactive activities.

The ENRICH program content and delivery approach was guided by Bandura's (2004) Social Cognitive Theory [53] and a chronic disease self-management approach [54]. Examples of social cognitive theory program constructs include: building self-efficacy (self-monitoring of behavior through use of step count diaries); identification of socio-cultural factors such as facilitators and impediments (brainstorming barriers and strategies to exercise when the weather is bad); outcome expectations (use and reflection of step count diaries); goal setting (setting and monitoring step count goal); and knowledge of risks and benefits (of PA, healthy eating and healthy weight management).

Traditional chronic disease self-management models encourage participants to take responsibility for their own health and behavior to make sustainable, life-long changes [54]. Chronic disease self-management has similar values to the core social cognitive theory constructs with key elements of chronic disease self-management being self-efficacy, motivation, developing achievable action plans, and role modelling [54].

